# Get BusActive!: Protocol of a single-blinded randomised controlled trial incentivising public transport use for physical activity gain among young people and adults

**DOI:** 10.1016/j.conctc.2024.101367

**Published:** 2024-09-11

**Keywords:** Transportation facilities, Behaviour and behaviour mechanisms, Economics, Exercise, Sedentary behaviour, Walking

## Abstract

**Background:**

Population level physical activity generally does not meet recommended targets. Compared with private motor vehicle users, public transport users tend to be more physically active and financial incentives may encourage more public transport use, but these relationships are under-investigated. This paper describes the protocol of a randomised controlled trial that aimed to determine the effect of financially incentivising public transport use on physical activity in a regional Australian setting.

**Methods:**

*Get BusActive!* is a 9.5-month single-blinded randomised controlled trial. A convenience sample of Tasmanians aged ≥15 years will be randomised to a 14-week incentive-based intervention (bus trip target attainment rewarded by bus trip credits and weekly supportive text messages) or an active control following baseline measures and will be followed up ∼24 weeks later (maintenance phase). Both groups will receive written physical activity guidelines. The primary outcome is change in accelerometer-measured steps/day from baseline to immediately post intervention phase and maintenance phase. Secondary outcomes are change in: smartcard-measured bus trips/week; measured and self-reported minutes/week of physical activity and sitting; transport-related behaviour (using one-week travel diary), perspectives (e.g. enablers/barriers) and costs; health. Linear mixed model regression will determine group differences. Participant-level process evaluation will be conducted and intervention cost to the public transport provider determined.

**Conclusion:**

*Get BusActive!* will fill an important knowledge gap about the causal relationship between financially incentivised public transport use and physical activity—the findings will benefit health and transport-related decision makers.

**Trial registration:**

ACTRN12623000613606.

**Universal trial number:**

U1111-1292-3414.

## Background

1

Continuation of current trends in physical inactivity is projected to result in 500 million new cases of non-communicable diseases and INT$520 billion in direct healthcare costs by 2030 [1]. Recent estimates show 81 % of 11–17 years and 27.5 % of adults globally do not meet physical activity targets [2,3]. Although non-communicable disease prevalence attributable to physical inactivity is estimated to be highest in low-middle income countries, the cost burden is proportionately greater in higher income countries [1].

Transport-related physical activity is receiving more attention in part because targeting leisure-time physical activity over the decades has not made measurable differences to population-level physical activity [4]. Fifteen minutes of daily physical activity reduces all-cause mortality risk by 14 %, cardiovascular disease risk by 19 %, ischemic heart disease risk by 25 % and increases life expectancy by three years, so short walks to and/or from public transport stops can be life-saving [5]. Transport-related physical activity also offers an important environmental co-benefits if it leads to less private motor vehicle use [6]. While transport-related physical activity is often discretionary, travelling from place to place (e.g. to/from work, school, services, shops, social/recreational activity) is a necessary behaviour for most. Dual process theory purports that individuals are likely to sustain physical activity if attached to a habitual pattern (i.e., travel) [7]. Yet evidence of effective and scalable strategies for increasing transport-related physical activity is sparse.

A 2012 review of nine studies (all observational conducted in the USA, UK and one in Australia) on physical activity associated with public transport use, showed that public transport users could accumulate an additional 33 min of daily walking [8]. Thus, using public transport can make an important contribution to weekly physical activity targets. In 2016 (census day), only 11.5 % of Australian commuters (employed people 15^+^ years) used public transport to get to work, which dropped to 4.6 % in 2021 likely due to the COVID-19 pandemic [9]. Consequently, there is plenty of scope to improve population level physical activity through public transport use. However, knowledge gaps remain regarding the causal relationship between public transport and physical activity and which strategies best increase transport-related physical activity.

Behavioural economics theory purports that price influences behaviour and choice [10,11]. There is some evidence that financial incentives (e.g. fare reduction) may positively influence behaviours such as physical activity and public transport use [[12], [13], [14], [15]]. There is also evidence of community support for financial incentives to increase public transport use, with a cross-sectional survey finding that financial incentives was rated third of 10 strategies most likely to increase public transport use in an Australian regional setting [16]. In the same setting, young people and people with a disability said that the cost of public transport was a barrier [17]. Taken together, financially incentivising public transport use and physical activity is a promising strategy for improving health, but randomised controlled trials are needed to establish effectiveness.

Responding to the evidence gap and an identified partner (a public transport provider, local and state government) need, in 2019 *trips4health* (an Australian based study) was the first randomised controlled trial to investigate the causal link between financially incentivised public transport and physical activity. However, *trips4health* was abandoned in mid-2020 due to substantial social and behavioural impacts of the COVID-19 pandemic. At trial cessation, one third (n = 110) of the target sample had completed a 16-week intervention (or equivalent control) phase, therefore providing only preliminary and process evaluation findings [18]. Financial incentives appeared to increase public transport use and transport-related physical activity, but the impact on total physical activity was less clear [19,20]. Although *trips4health* demonstrated strong fidelity and feasibility, process evaluation data highlighted that some population groups were under-represented (e.g. men, and those less educated) and some aspects of the intervention could be improved [18].

*Get BusActive!* builds on preliminary and process evaluation findings from *trips4health* and partner feedback and has refined inclusion criteria, recruitment approaches, outcome measures and data collection methods. Co-design processes with consumers/community and end-users are embedded to support study participation and subsequent scale-up. *GetBusActive!* aims to determine the causal relationship between financially incentivised public transport and physical activity and its longer-term impacts in a regional setting.

## Objectives/Hypothesis

2

The primary hypothesis is: A public transport incentives scheme will increase daily steps (accelerometer-measured) compared to a control group. Secondary hypotheses are: A public transport incentives scheme will increase public transport use (objectively measured) and transport-related physical activity (self-reported) compared to a control group.

## Trial design

3

Single-blinded parallel group randomised controlled trial.

## Materials and methods

4

### Study setting

4.1

The study will occur in Tasmania, Australia. Tasmania is an island state with a population of approximately 555,000 (460,344 ≥ 15 years). Public transport is provided predominantly by bus, mostly by Metro Tasmania, with services delivered in three of the main population centres—Greater Hobart (population: 226,653), Launceston (population: 90,953) and Burnie (population: 19,919) [21] (Fig. 1). Tasmania has one of the lowest rates of public transport use in Australia with only 3 % and 3.2 % of employed people 15 years^+^ using public transport to get to work in 2016 and 2021 respectively [9]. Unequal and inequitable access to Tasmanian public transport and limitations in service provision contribute to low patronage [17,22,23]. Further, only 26 % of Tasmanians (15^+^ years) self-reported meeting weekly physical activity targets in 2021 [24].

**Fig. 1 fig1:**
[figure not shown]
Study setting.

### Eligibility criteria

4.2

Potential participants will be screened by online survey or telephone. The self-assessed inclusion and exclusion criteria are listed in Box 1. Those eligible will receive an information sheet and provide online or verbal consent.Box 1Self-assessed inclusion and exclusion criteria**Table undtbl1:** 

Inclusion criteria
• ≥ 15 years
• Tasmanian resident
• sufficient English proficiency to provide informed consent
• possession of a mobile phone and active email address
• ownership of or willingness to obtain a Metro Greencard (travel smartcard)
• willingness to give permission for the researchers to access smartcard data
• currently making no more than five Metro bus trips/week
• able to reasonably access a Metro bus service
• currently making trips by motor vehicle (including motorcycle) that could be made by bus
Exclusion criteria
• intending to move house or work location within the study period whereby a Metro bus service will be inaccessible
• currently engaged in or planning to engage in other public transport incentives program
• pregnancy
• a health condition that prevents walking
• a health condition that prevents bus use
• a planned activity that would prevent bus use for greater than four weeks during the 14-week intervention phase of the 38-week study period (e.g. surgery, extended holiday)Alt-text: Box 1

### Interventions

4.3

The intervention group will receive a 14-week intervention whereby they are financially incentivised with smartcard credit to meet weekly bus trip targets, supplemented by weekly supportive text messages (Table 1). Intervention participants will also receive Australia's physical activity and sedentary behaviour guidelines for adults (≥18 years) or for young people (<18 years), as relevant [25,26]. *Get BusActive!* is based on the *trips4health* protocol but with enhancements informed by preliminary and process evaluation findings [[18], [19], [20],^27^]. Using a gain-framed approach (rewarding positive behaviours), targets increase progressively, with corresponding incentive increases. *trips4health* data indicated a levelling out in target attainment beyond three trips/week, so a maximum trip increase target of three/week is scheduled, with a stretch goal of four/week [19]. While there is no consensus on minimum time for habit formation, at least 66 days (9.4 weeks) are likely needed [28]. Subsequently, a 14-week intervention phase has been chosen which allows 10 weeks for habit formation and four weeks for maintenance (‘tapering off’), where contact and support is gradually withdrawn in preparation for intervention cessation [28].

**Table 1 tbl1:** *Get BusActive!* intervention schedule.

	Intervention phase	Bus trip target increase p/wk	Incentive – bus trip credits	$ value (all zones Child/student^a^)	$ value (all zones Adult)	$ value (all zones Adult concession)	Text message frequency
Week 1	Getting started	1	1	1.52	5.76	1.92	x 2
Week 2	Getting started	1	1	1.52	5.76	1.92	x 2
Week 3	Getting started	1	1	1.52	5.76	1.92	x 2
Week 4	Building up	2	2	3.04	11.52	3.84	x 2
Week 5	Building up	2	2	3.04	11.52	3.84	x 2
Week 6	Building up	2	2	3.04	11.52	3.84	x 2
Week 7	Moving along	3	3	4.56	17.28	5.76	x 2
Week 8	Moving along	3	3	4.56	17.28	5.76	x 2
Week 9	Moving along	3	3	4.56	17.28	5.76	x 2
Week 10	Aiming high	4	5	7.60	28.8	9.6	x 2
Week 11	Maintenance	3	3	4.56	17.28	5.76	x 2
Week 12	Maintenance	3	3	4.56	17.28	5.76	x 2
Week 13	Tapering	3	2	3.04	11.52	3.84	x 1
Week 14	Tapering	3	1	1.52	5.76	1.92	x 1
***Total***		**34**	**32**	**$48.64** (AUD)	**184.32** (AUD)	**$61.44** (AUD)	**28**

Value of incentive = cost of participant’s usual fare type times number of bus trip credits allocated aeligible for child/student fare up until end of year in which passenger turns 18 years old.

To assist participants in achieving weekly targets and consistent with best practice, incentives will be supported by weekly text messages (two per week for weeks 1–12 and once per week in weeks 13 and 14) that target other behaviour change techniques (e.g. planning, goal setting) [29]. Text messages may help counter the potential risk that incentives alone could undermine intrinsic motivation in the absence of broader behavioural support [30]. In *trips4health*, text messages were well-received, but some participants recommended personalising the messages to increase salience and impact–consequently text messages will be co-designed with end-users and informed by habit formation theory [28,31], the Behaviour Change Technique Taxonomy [32], our previous qualitative work [16,33] and a relevant incentive-based study targeting leisure-time physical activity [12].

Active control participants will receive the same physical activity guidelines as outlined for the intervention group [25,26]. Cognitive strategies such as providing physical activity guidelines are unlikely to influence physical activity behaviour [34]—the guidelines will be provided to help engage and retain participants.

### Outcomes

4.4

The primary and secondary outcomes and timing of measures are summarised in Table 2. The primary outcome is change in accelerometer-measured average daily step count (steps/day) over seven days. There are 15 secondary outcomes relating to travel behaviour and perspectives, physical activity, sedentary time (sitting), health, transport behaviour economics and intervention implementation costs.

**Table 2 tbl2:** Primary and secondary outcomes and timing of measures.

Outcome (change in …)	Timing of measure	T1	T1-T2	T2	T3
Primary outcome					
Accelerometer measured steps/day averaged over seven days		X		X	X
Secondary outcomes					
Accelerometer measured minutes/week of physical activity		X		X	X
Accelerometer measured minutes/week of sitting		X		X	X
Smartcard measured bus trips/week			X	X	X
Smartcard measured costs to public transport provider			X		
Self-reported (travel diary) trips/week by mode, frequency and duration		X		X	X
Self-reported (travel diary) commute time/week by mode		X		X	X
Self-reported (survey) perspectives on travel behaviour (e.g. enablers/barriers)		X		X	X
Self-reported (survey) out of pocket transport-related expenses		X		X	X
Self-reported (survey) work productivity		X		X	X
Self-reported (survey) commute time to work/study		X		X	X
Self-reported (survey) commute by mode to work/study		X		X	X
Self-reported (survey) physical activity minutes/week by type (transport, leisure, occupational, domestic, total)		X		X	X
Self-reported (survey) sitting hours/day		X		X	X
Self-reported (survey) body mass index via self-measured height and weight		X		X	X
Self-reported (survey) health		X		X	X

T1/Timepoint 1: Baseline; T2/Timepoint 2: Immediately after completion of the14-week intervention phase (∼week 15); T3/Timepoint 3: Immediately after completion of the 24-week maintenance phase (∼week 39).

### Participant timeline

4.5

The participant flowchart is summarised in Fig. 2.

**Fig. 2 fig2:**
[figure not shown]
Participant flowchart.

### Sample size

4.6

At least 345 participants will be randomly allocated across both study arms—an oversampling of 15 % to allow for attrition (based conservatively on *trips4health* and the relevant ACHIEVE study [12,18]) leaving a minimum of 300 participants. Three hundred participants will provide 80 % power (two-sided α = 0.05) to detect a 34 % change (∼2500 steps/day) in daily steps in the intervention group relative to controls (primary outcome) and meaningful increases (13–29 %) in secondary outcomes. The power calculation is based on the standard deviation of change in the physical activity outcomes, log-transformed due to the right-skewed nature of physical activity data (Table 3).

**Table 3 tbl3:** Increase in outcomes detected with n = 300.

Outcomes	Standard deviation of change (log scale)^a^	Relative increase in outcome
Accelerometer (steps/day)	0.336	11.5 %
Transport-related physical activity (hours/week)	0.790	29.1 %
Bus use in week (trips/day)	0.390	13.4 %

a Standard deviation estimates from *trips4health*.

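### Section 4.6 gives the detectable effect on steps/day as 34 % (about 2500 steps), but Table 3 gives 11.5 %, and only 11.5 % follows from the stated inputs

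*Protocol article*

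**What the plan says.** Section 4.6 (Sample size) of the protocol article makes two statements about the effect on the primary outcome that the trial can detect.

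- **Text.** For 300 participants the text claims 80 % power, testing two-sided at the 5 % level. The effect this refers to is worded as follows: "to detect a 34 % change (∼2500 steps/day) in daily steps in the intervention group relative to controls (primary outcome"). The sentence goes on to claim power for "meaningful increases (13–29 %) in secondary outcomes".
- **Table 3.** The title is "Increase in outcomes detected with n = 300", and the row for the primary outcome reads "Accelerometer (steps/day) 0.336 11.5" %. The middle number is the standard deviation of change on the log scale, and the last is the relative increase.

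The text presents the table as the basis of its claim: "The power calculation is based on the standard deviation of change in the physical activity outcomes, log-transformed". The sample of 300 is the number expected to remain after attrition ("leaving a minimum of 300 participants"). Section 4.8 sets allocation at 1:1.

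**The concern.** The text and the table describe the same outcome, the same number of participants and the same calculation, yet give 34 % and 11.5 %. The secondary range in the text agrees with the other two rows of Table 3 (13.4 % and 29.1 %), so the disagreement is confined to the primary outcome.

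This is the only sentence in the article's text that states power for the primary outcome. Taken at face value, it says the trial is sized only for very large effects, around 2500 steps/day. That sets a wrong benchmark for the result: a real gain of the size the trial was designed to find would look like a failure against the published target. The figure could also be reused in later reports or in planning another trial.

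**Working it through.** **Inputs, all from the protocol article**

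- Analysed sample 300 (section 4.6); 1:1 allocation (section 4.8), so 150 per arm.
- Power 80 %, two-sided α = 0.05 (section 4.6): z = 1.960 and 0.8416, sum 2.8016.
- Log-scale standard deviation of change (Table 3): steps 0.336; transport-related physical activity 0.790; bus use 0.390.

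**Step 1. Reproduce Table 3**

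For a comparison of mean log change between two equal arms:

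δ = (z₀.₉₇₅ + z₀.₈₀) × SD × √(2/150); relative increase = exp(δ) − 1

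| Outcome | SD | δ | Recomputed | Table 3 |
|---|---|---|---|---|
| Steps/day | 0.336 | 2.8016 × 0.336 × 0.11547 = 0.1087 | 11.5 % | 11.5 % |
| Transport-related physical activity | 0.790 | 0.2556 | 29.1 % | 29.1 % |
| Bus use | 0.390 | 0.1262 | 13.4 % | 13.4 % |

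All three rows reproduce, so this is the method behind the table. A t-based calculation also gives 11.5 % for steps. In reverse, ln(1.115) with SD 0.336 needs 150 per arm.

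**Step 2. Test the 34 %**

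ln(1.34) = 0.2927.

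- Sample needed at SD 0.336: 2 × (2.8016 × 0.336 / 0.2927)² = 20.7 per arm, so 21 per arm or 42 in total (22 per arm if t-based).
- Power with 150 per arm: 0.2927 / (0.336 × 0.11547) = 7.54; 7.54 − 1.96 = 5.58; power above 99.99 %.
- SD at which 34 % would be the 80 %-power effect with 300: 0.2927 / (2.8016 × 0.11547) = 0.905, against the stated 0.336.

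**Step 3. Look for a variant that gives 34 % for steps**

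| Variant | Detectable increase |
|---|---|
| One-sided α = 0.05 | 10.1 % |
| 90 % power | 13.4 % |
| All 345 randomised participants analysed | 10.7 % |

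None comes near 34 %.

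**Step 4. Steps/day equivalent**

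The article states no baseline step count. If 2500 was computed as 34 % of baseline, the baseline is 2500 / 0.34 ≈ 7350, and 11.5 % of it is about 845 steps/day. The 2500 cannot plausibly belong with 11.5 % instead, because that would imply a baseline of 2500 / 0.115 ≈ 21,700 steps/day.

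As a side check on plausibility, Table 1 schedules three extra trips a week for most of the later weeks. If all the gain came from those trips, 2500 steps/day would mean 2500 × 7 / 3 ≈ 5800 steps per extra trip.

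**The case against.** The strongest reply is that little turns on the error. The correct figure stands in Table 3 within the same section, and the sample size, primary outcome and analysis model are unaffected. The error understates what the trial can detect, so the trial is not underpowered for the claim as written. What a null result excludes will be read from its confidence interval, not from a planned detectable effect. All of this is fair and limits the harm to reporting and interpretation. It does not make the sentence true, and a reader who takes the design target from the text gets the wrong number for the primary outcome.

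A second reply is that 34 % may be a separate target effect rather than the smallest detectable one. The sentence rules that out as a defence, because it ties 34 % to 80 % power with 300 participants; at the stated standard deviation the power would be above 99.99 %.

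Two cautions stand. First, the origin of the 34 % is unknown. It is close to the standard deviation itself (0.336), which suggests that the standard deviation was copied in as the effect, but it is also close to 0.115 / 0.336 = 0.34, a standardised effect written as a percentage. The article does not settle this, and the point does not depend on it. Second, the 7350 and 845 figures are derived from the same 34 % and 2500 pair that is in doubt, so they are illustrative. The per-trip figure is likewise only a plausibility aside.

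**Conclusion.** The concern holds. The text of section 4.6 contradicts Table 3 on the primary outcome, and only the table's 11.5 % follows from the stated sample size, standard deviation, power and significance level. The text overstates the detectable effect by a factor of about three (34 / 11.5 = 2.96).

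The conclusion rests on 300 analysed participants split equally, a log-scale standard deviation of change of 0.336, and the two-sample comparison of mean log change that reproduces every row of Table 3. The percentage discrepancy needs no outside assumption. Only the conversion to about 845 steps/day does, namely that 2500 was meant as 34 % of baseline. The error must be corrected because it is the power statement for the primary outcome, but it gives no reason to change the number of participants.

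**What to change.** In the text of section 4.6, replace the 34 % and the 2500 steps/day with an 11.5 % relative increase, in agreement with Table 3. Give the steps/day equivalent as 11.5 % of the actual baseline mean from the earlier trial, and state that baseline. About 845 steps/day applies only if the baseline is near 7350. If 34 % was intended as a separate anticipated effect, label it as such, give its source and detach it from the claim of 80 % power.

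Check any registry entry, statistical analysis plan or report that quotes the power statement, and correct it there if the figure was repeated. The cost is one sentence; the sample size, design and analysis stay as they are.

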### Recruitment

4.7

In *trips4health* there was an over-representation of females (69 %) and those university educated (55 %) compared with the Greater Hobart population where the study was located (52 % females, 17 % university educated) [18]. A consumer advisory group will co-design recruitment approaches and materials for *Get BusActive!* to maximise participant reach and diversity. The consumer advisory group (chaired by a lead investigator) will comprise 6–10 diverse members from the study area.

A range of recruitment methods will be used e.g. social and traditional media, the Metro website and Metro bus advertising, cross-promotion via other relevant surveys, Tasmanian Government staff newsletter; University of Tasmania (UTAS) staff intranet; local government (particularly councils in the catchment area); libraries and relevant community-based organisations and advising participants from our previous transport-related studies who had indicated their interest to be informed of future projects. Interested individuals will be directed to a study website or telephone number for screening.

To support recruitment and retention, participants will be compensated (in the form of a gift card) for completing each of the three assessments—T1 = $20 gift card; T2 = $35 gift card; T3 = $45 gift card (total $100). Another retention strategy is allowing pauses in study participation for up to four weeks in total (minimum one week for each pause) during the 14-week intervention period if circumstances preventing bus use arise (e.g. travel, prolonged illness).

